### Adherence to the study protocol

Assumptions regarding transfusion rates in the two groups were made in calculating the sample size [7]; if transfusion rates do not match these assumptions, the power of the study will be reduced. Therefore, measuring and assessing adherence with the transfusion protocol is critical. Non-adherence is defined in two ways: (a) the patient received a RBC transfusion outside of the protocol (‘extra’ transfusion) and (b) the patient was not given a RBC transfusion that, according to the protocol, should have been given (‘withheld’ transfusion). Adherence will be assessed for the period from randomization to hospital discharge, although if a patient withdraws or has treatment discontinued, adherence after the time of withdrawal or discontinuation will not be assessed. For both types of non-adherence, instances will be classified as mild, moderate or severe (see Table 1), according to the likely influence on transfusion rates, and therefore possible influence on study outcomes.

**Table 1 Tab1:** **Non-adherence to transfusion protocol**

	**Transfusion outside of protocol**	**Transfusion according to protocol withheld**
Mild	Not applicable	A transfusion took place, but more than 24 hours after the breach of the relevant transfusion threshold
Moderate	Patient transfused, but patient did breach the relevant threshold for transfusion at some point postoperatively (before or after the transfusion outside of protocol)	Patient was not transfused following a breach, but the patient had previously had at least one post-randomization transfusion
Severe	Patient transfused, and patient did not breach the relevant threshold for transfusion at any point postoperatively	Patient was not transfused following a breach, and patient had no post-randomization transfusions

A patient can breach the relevant threshold for transfusion several times, and so there can be more than one case of non-adherence per patient.

The frequency of each type of non-adherence will be described by treatment allocation. Further descriptive analyses will be undertaken, to look at non-adherence in more detail, including: reasons for non-adherence, number of deviations from the protocol per patient, haemoglobin or haematocrit levels at deviations and the day of the week and time of the day of deviations. Characteristics of patients with or without any non-adherence will be compared and non-adherence rates will be described by site.

### Statistical analysis principles

Analysis principles and presentation of data will follow the guidance issued in the CONSORT statement [10].

### Descriptive data

Pre-randomization characteristics (for example, patient demography, intra-operative details and pre-randomization RBC transfusions) will be described by treatment allocation for patients in the analysis population. Continuous variables will be summarized using the mean and standard deviation (or median and interquartile range if the distribution is skewed), and categorical data will be summarized as a number and percentage. Any imbalances in the characteristics of the patients will be described but statistical tests for imbalance will not be carried out in line with recommendations [10]. In addition, available characteristics will be described by: (a) non-consented and consented patients and (b) consented but not randomized (because threshold was not breached) and randomized patients (including pre- and intra-operative characteristics, transfusions, haemoglobin levels, EQ5D data and mortality).

### Outcome data

All outcomes listed in the study protocol will be analyzed under the umbrella of one of four types of outcome: (a) binary, (b) continuous, (c) time to event and (d) continuous longitudinal. Table 2 classifies each outcome.

**Table 2 Tab2:** **Classification of primary and secondary outcomes**

**Category**	**Outcomes**
Binary outcome measures	• Primary outcome measure: proportion of patients experiencing an infectious or ischaemic event
	The following secondary outcome measures:
	• Proportion of patients experiencing an infectious event
	• Proportion of patients experiencing an ischaemic event
	• Use of activated factor seven
	• Use of Human Blood Coagulation Factor IX
	• Significant pulmonary morbidity
Continuous outcome measures	The following secondary outcome measures:
	• Units of RBCs transfused
	• Fresh frozen plasma transfusions
	• Cryoprecipitate transfusions
	• Platelet transfusions
Time-to-event outcome measures	The following secondary outcome measures:
	• Time from randomization to first occurrence of the primary outcome measure (secondary analysis of the primary outcome measure)
	• Duration of post-randomization stay in intensive care or high dependency unit
	• Duration of post-randomization hospital stay
	• Time from randomization to death from any cause
Continuous longitudinal outcome measures	The following secondary outcome measures:
	• EQ5D single summary index score
	• EQ5D visual analogue scale score

General presentation and analysis techniques for each type of outcome are described next.

#### Binary outcomes

The numbers and percentages of patients experiencing each outcome will be presented by treatment group and compared using logistic regression. Formal statistical comparisons of treatment effects will only be performed if more than ten patients in total experience the outcome (with at least one event in each treatment group). Treatment comparison estimates will be presented as adjusted odds ratios and 95% confidence intervals.

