### Sample size

Based on previous data [1] and allowing for anticipated non-adherence to the allocated thresholds [7], the primary outcome frequencies were hypothesized to be 17% and 11% in the liberal and restrictive groups. A sample size of 1,468 was required to detect this difference with 90% power and 5% significance (two-sided test). The target sample size was inflated to 2,000 to allow for uncertainty about non-adherence, since higher than expected non-adherence would reduce power. Full details are reported elsewhere [7].

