### Statistical significance

For hypothesis tests, two-tailed *P* values <0.05 are considered statistically significant. Likelihood ratio tests will be used in preference to Wald tests for hypothesis testing.

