### Multiple testing

No formal adjustment will be made for multiple testing. However, the following measures to avoid problems with over-interpretation will be taken: (a) formal statistical comparisons will not be made for outcomes with low event rates, and (b) only pre-specified subgroup analyses will be performed and a significance level of 5% will be used for the tests for interaction for subgroup analyses despite being low powered tests. Consideration will be taken in the interpretation of results to reflect the number of statistical tests performed and the consistency, magnitude and direction of treatment estimates for different outcomes.

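### A binary outcome with more than ten events gets no test and no interval if all its events fall in one arm (minor; mainly two rare secondary outcomes)

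*SAP article*

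**What the plan says.** The Binary outcomes section of the SAP article plans logistic regression for every binary outcome and sets a gate in front of it: formal comparisons "will only be performed if more than ten patients in total experience the outcome (with at least one event in each treatment group"). For outcomes that pass, "Treatment comparison estimates will be presented as adjusted odds ratios and 95% confidence intervals". This is the only interval planned for a binary outcome. The descriptive part carries no condition on counts: "The numbers and percentages of patients experiencing each outcome will be presented by treatment group".

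Two other sections bear on the rule. Multiple testing lists, among its measures against over-interpretation, that "formal statistical comparisons will not be made for outcomes with low event rates". Statistical significance sets the level (two-tailed P "values <0.05 are considered statistically significant") and states: "Likelihood ratio tests will be used in preference to Wald tests for hypothesis testing".

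Table 2 lists six binary outcomes: the primary outcome, its infectious and ischaemic parts, use of activated factor seven, use of Factor IX, and significant pulmonary morbidity. No method is named for an arm with no events. The Model assumptions section allows other methods when assumptions fail, but it does not lift the explicit gate under Binary outcomes.

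**The concern.** The two conditions differ in kind. The total count depends only on pooled data, so it can be applied without knowing which arm the events came from. The bracketed condition depends on how the events divide between the arms, which is the treatment difference itself. It acts in the wrong direction: for a given total above ten, it removes only the most one-sided table and leaves every weaker imbalance open to testing.

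The likely reason is technical. With an empty arm, the maximum-likelihood odds ratio is zero or infinite and its Wald interval does not exist. That limits one estimator. It does not mean that the arms cannot be compared.

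At stake is a rare binary secondary outcome whose events all fall in one arm. The plan would then print counts and percentages only, while a nearly balanced split with the same total would be tested.

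**Working it through.** **Inputs.** Target of 2,000 patients (Sample size) allocated 1:1 (Methods and Design). I assume an even split of 1,000 per arm. The gate is more than ten events in total and at least one per arm (Binary outcomes).

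**Check of the design figures.** The plan states that "the primary outcome frequencies were hypothesized to be 17% and 11% in the liberal and restrictive groups" and that "A sample size of 1,468 was required to detect this difference with 90% power and 5% significance (two-sided test"). The usual two-proportion formula gives

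n = [1.960·√(2 × 0.14 × 0.86) + 1.282·√(0.17 × 0.83 + 0.11 × 0.89)]² / 0.06² = 701 per arm, 1,402 in total.

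With the continuity correction, (n/4)·[1 + √(1 + 4/(0.06n))]² = 734 per arm, or 1,468 in total. The stated figure reproduces. It does not bear on the gate and only confirms the inputs.

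**What the gate does at its smallest total, 11 events, 1,000 per arm.** P is Fisher's two-sided exact value. The interval is the exact conditional 95% interval for the odds ratio, arm with fewer events against arm with more.

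| Split | Fisher P | Exact 95% interval for OR | Formal comparison under the plan |
|---|---|---|---|
| 2 vs 9 | 0.065 | 0.023 to 1.07 | yes |
| 1 vs 10 | 0.0115 | 0.002 to 0.70 | yes |
| 0 vs 11 | 0.00095 | 0 to 0.396 | no |

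The bar continues at larger totals: 0 vs 12 gives P = 0.00047, and 0 vs 15 gives P = 0.00006. The result does not depend on the assumed arm size: with 734 per arm, 0 vs 11 gives P = 0.00094 and an upper limit of 0.395.

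**How unusual the barred table is under no effect.** Each of 11 events falls in either arm with probability about one half, so one arm is empty with probability about 2 × 0.5¹¹ = 0.001.

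**Whether the bracket is needed for a test.** The unadjusted likelihood ratio statistic, the type of test that the plan prefers, is finite with a zero cell:

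G = 2 × [11·ln(0.011) + 989·ln(0.989) − 11·ln(0.0055) − 1989·ln(0.9945)] = 15.3, P = 0.00009.

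The profile-likelihood upper limit for the odds ratio is about 0.19. Both rest on a large-sample approximation that is rough with an empty cell, so the exact figures are the safer ones. The risk difference needs no special handling: 11/1,000 − 0/1,000 = 1.1 percentage points, Newcombe score-type 95% interval 0.48 to 1.96.

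**Reach.**

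- Primary outcome: the chance of no events among 1,000 patients at 11% is 0.89¹⁰⁰⁰, about 2 × 10⁻⁵¹. With 734 patients it is about 7 × 10⁻³⁸. Its infectious and ischaemic parts are very unlikely to have an empty arm.
- Death: analysed as time to event (Table 2), outside this gate.
- Adverse events: the Safety data section plans no formal comparison whatever the split.
- Factor seven and Factor IX use: the document gives no rates, so any probability is an assumption. With true rates by arm of 0.05% and 1.5%, the chance of 0 vs 11 or more is 54%. With 0.1% and 1.0% it is 15%, and with 0.2% and 1.5% it is 12%. These pairs are ratios of 30, 10 and 7.5.

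**The case against.** The best defence is that the bracket is an ordinary estimability condition. The plan's measure is an adjusted odds ratio, and with an empty arm there is no finite estimate to present. The clause can only withhold a comparison, so it cannot create a false-positive claim. This explains the clause, but it does not justify making no comparison at all when exact and penalized methods exist.

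The defence is right about size. The assumed rates that make the barred table at all likely need a ratio of 7.5 to 30 between arms, and nothing in the document suggests that a red-cell threshold has such an effect on clotting-factor use.

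Three stronger readings are tempting, and the document does not support them:

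- That the rule suppresses harms. Adverse events are excluded from formal comparison by the Safety data section in any case, so the bracket changes nothing for them.
- That it hides a real difference. Numbers and percentages by arm are planned without condition, so 0/1,000 versus 11/1,000 would be visible. Only the P value and interval would be missing.
- That the plan presents the one-event-per-arm clause as a safeguard against over-interpretation. Multiple testing speaks only of low event rates, which the more-than-ten condition already covers, and does not mention the clause.

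It is also true that an exact fallback loses the planned adjustment, for operation type as well as for centre. That is a fair cost and should be stated.

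**Conclusion.** The point holds, and it is minor. As written, the gate bars the most one-sided table at any total above ten and permits weaker ones: 1 vs 10 with P = 0.0115 is compared, and 0 vs 11 with P = 0.00095 and an odds ratio interval of 0 to about 0.40 is not. The decision to test therefore depends on the result by arm, in the wrong direction.

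The figures assume 1,000 patients per arm and are unadjusted. The practical reach is mainly use of activated factor seven and use of Factor IX, and whether either would ever meet the condition cannot be judged from the document. For significant pulmonary morbidity the document gives no rate either, and I do not claim that it is affected. No conclusion on the primary outcome, mortality or safety depends on the clause. The more-than-ten rule is a defensible choice and is not criticized here.

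**What to change.** Under Binary outcomes, keep the condition of more than ten events in total and delete the bracket. Add one rule: if one arm has no events, report Fisher's exact P value with an exact or score-type interval for the risk difference, or a Firth odds ratio with its profile-likelihood interval. Choose one of the two in advance, and state that this fallback comparison is not adjusted for operation type or centre.

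The cost is a sentence or two of text and routine software, plus the loss of adjustment in this one situation. A Firth model that kept the random centre effect would be more work, and for a rare secondary outcome it is not needed. The Discussion reports that the analysis has already been carried out, so for this trial the change could only affect how such a table is reported. It also says that the trials unit revised its plan template after a comment on imputation, and this rule could be corrected there in the same way.

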#### Continuous outcomes

These will be summarized by the mean and standard deviation (or median and interquartile range if data are skewed) in each treatment group and compared using linear regression. For untransformed data, treatment comparisons will be presented as adjusted differences in means with 95% confidence intervals, and for logarithmically transformed data as adjusted ratios of geometric means with 95% confidence intervals. If a logarithmic transformation is not satisfactory other analysis or presentation methods will be sought.

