## Update

This paper provides the detailed statistical analysis plan for the Transfusion Indication Threshold Reduction (TITRe2) randomized controlled trial, comparing transfusion rates, morbidity and healthcare resource use following two different transfusion strategies after cardiac surgery.

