### Outcomes

The primary outcome measure is a binary composite outcome of any serious infectious (sepsis or wound infection) or ischaemic (permanent stroke, myocardial infarction, acute kidney injury or gut infarction) event in the first 3 months after randomization. Full details of qualifying events and the manner in which they will be verified are available in the protocol [7].

Secondary outcome measures are:Units of RBCs and other blood components transfused during a participant’s hospital stay,Proportion of patients experiencing an infectious event,Proportion of patients experiencing an ischaemic event,EQ5D [9],Duration of postoperative stay in intensive care or high dependency unit,Duration of postoperative hospital stay,All-cause mortality,Significant pulmonary morbidity, comprising: (a) initiation of non-invasive ventilation (for example, continuous positive airway pressure ventilation), (b) reintubation/ventilation, or (c) tracheostomy,Cumulative resource use, cost and cost-effectiveness. (This analysis is being undertaken by the Health Economics Research Centre at the University of Oxford and is not covered in this statistical analysis plan.)

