**Flow of participants.**

Participants consent to the study before surgery if they meet all of the pre-consent eligibility criteria (see Figure 1) and give written consent. They are then randomized if at any point post-surgery they meet the post-consent eligibility criteria (haemoglobin concentration falls below 9 g/dl or haematocrit below 27%). This means that a significant proportion of patients (estimated to be approximately 30% from earlier studies [1]) consent to the study but are not randomized. Randomized patients should be given a RBC transfusion as soon as possible after haemoglobin or haematocrit levels breach the relevant thresholds, and at most within 24 hours.

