### Model assumptions

For all methods outlined, underlying assumptions will be checked using standard methods, for example, residual plots or log-log plots for proportional hazards. If assumptions are not valid, alternative methods of analysis will be sought (for example, by applying a logarithmic transformation or fitting a two-part mixed model for semi-continuous data [11]). If extreme outlying observations are found, whereby inclusion of such values results in an inadequate model fit, such observations will be excluded from the main analyses and sensitivity analyses may be performed to examine the effect on the study’s conclusions.

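### If residual checks fail, the analysis of red cell units is left open to methods that zero units make undefined or non-randomized; one all-patient mean comparison should be fixed instead

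*SAP article*

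**What the plan says.** The Outcomes section lists as a secondary outcome "Units of RBCs and other blood components transfused during" the hospital stay. Table 2 places "Units of RBCs transfused" under continuous measures. Plasma, cryoprecipitate and platelet transfusions are the only other entries in that class.

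The Continuous outcomes section specifies linear regression and reporting in this order:

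- The default comes first: "For untransformed data, treatment comparisons will be presented as adjusted differences in means with 95% confidence intervals".
- The log option comes second: "for logarithmically transformed data as adjusted ratios of geometric means with 95% confidence intervals".
- An open-ended fallback comes third: "If a logarithmic transformation is not satisfactory other analysis or presentation methods will be sought".

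The Model assumptions section adds that, where assumptions do not hold, alternatives will be found, for example "by applying a logarithmic transformation or fitting a two-part mixed model for semi-continuous data".

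On entry to the trial, the Flow of participants section says that consented patients are randomized if, after surgery, "haemoglobin concentration falls below 9 g/dl or haematocrit below 27" per cent. Methods and Design gives the same two values as the liberal transfusion threshold; the restrictive threshold is 7.5 g/dl or 22%.

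The Time-to-event section has a rule for times of zero (half the smallest non-zero time). No rule is given for zero units.

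**The concern.** The entry criterion equals the liberal trigger. An adherent liberal patient is therefore due a transfusion on randomization, while an adherent restrictive patient who never reaches the lower threshold receives no RBC unit afterwards. Zero units are thus a result of the intervention, expected mainly in one arm, and this could be foreseen at design.

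Skewed counts with many zeros may well fail a residual check. The analyst would then choose, with the data in view, among a log that cannot be taken at zero, a two-part model for which no overall effect measure is named, and a method not yet named. These can give materially different answers. The outcome also shows whether the two strategies separated in blood use, which the article's opening statement of purpose puts first: "comparing transfusion rates, morbidity and healthcare resource use".

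**Working it through.** The document states no figure for transfused units, so there is nothing of the plan's own to reproduce. It also gives no transfusion rates by arm. **Every distribution below is an assumption chosen to show the mechanism, not an estimate for this trial.**

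**Illustration A: one unit saved in every patient.** Liberal units are 1, 2, 3, 4, 5 with probabilities 0.40, 0.30, 0.15, 0.10, 0.05. Restrictive units are liberal units minus 1.

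- Liberal mean: 0.40 + 0.60 + 0.45 + 0.40 + 0.25 = 2.10.
- Restrictive mean: 0 + 0.30 + 0.30 + 0.30 + 0.20 = 1.10.
- All-patient ratio: 1.10 / 2.10 = 0.52; difference −1.00 unit.
- Positive part only: 60% of restrictive patients have any unit, with mean 1.10 / 0.60 = 1.83. Ratio 1.83 / 2.10 = 0.87. On the geometric scale it is 1.60 / 1.81 = 0.89.
- Log with added constant c: ratio = exp[Σ p·log(u − 1 + c) − Σ p·log(u + c)], where u is liberal units.

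| c | restrictive | liberal | ratio |
|---|---|---|---|
| 1 | 1.81 | 2.90 | 0.62 |
| 0.5 | 1.20 | 2.36 | 0.51 |
| 0.1 | 0.55 | 1.92 | 0.29 |
| 0.01 | 0.21 | 1.82 | 0.12 |

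The same data give a reduction of 38% or 88%, depending only on c.

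**Illustration B: heavier tail, same one-unit saving.** Liberal units are 1, 2, 3, 4, 6, 10 with probabilities 0.50, 0.20, 0.10, 0.10, 0.05, 0.05.

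- Liberal mean: 0.50 + 0.40 + 0.30 + 0.40 + 0.30 + 0.50 = 2.40. Restrictive mean: 1.40. Ratio 1.40 / 2.40 = 0.58.
- Positive part: 50% transfused, mean 1.40 / 0.50 = 2.80; 2.80 / 2.40 = 1.17. The direction reverses although every patient gains.

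**Illustration C: some liberal patients also untransfused.** 90 to 95% of liberal and 30 to 60% of restrictive patients receive any unit. Units among the transfused are 1 + Poisson(1) in the liberal arm and 1 + Poisson(m) in the restrictive arm, with m = 1 or 1.5. The arm mean is P(any) × (1 + m).

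- All-patient ratio: from (0.30 × 2) / (0.95 × 2) = 0.32 to (0.60 × 2.5) / (0.90 × 2) = 0.83. Differences run from −1.30 to −0.30 units.
- Ratio of means among the transfused: 2 / 2 = 1.00 or 2.5 / 2 = 1.25. The saving vanishes or reverses.
- For 90% against 50% with m = 1, the all-patient ratio is 1.00 / 1.80 = 0.56; the log ratio is 0.66, 0.54 and 0.31 for c = 1, 0.5 and 0.1.

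**Combining the two parts.** Multiplying the ratio of proportions transfused by the positive-part ratio recovers the all-patient ratio: A, 0.60 × 0.87 = 0.52; B, 0.50 × 1.17 = 0.58. The distortion comes from reading the positive part alone, not from the two-part model as such.

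**The case against.** The case for leaving the plan as it is has real weight.

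- Untransformed linear regression comes first. It is defined with zeros, includes all analysed patients, and with about 1,000 per arm usually tolerates skew. That a residual check will fail is likely, not certain.
- Nothing instructs the analyst to drop zeros or add a constant, and an unsatisfactory log leads to other methods.
- The two-part model is only an example, is a recognised approach to data with many zeros, and shows that zeros were foreseen. Its binary part is a randomized comparison of any transfusion.
- Haemoglobin thresholds create arm-dependent zeros for RBCs only, not for plasma, platelets or cryoprecipitate.
- The Outcomes section counts units over the hospital stay without saying whether pre-randomization units are included. If they are, there are fewer zeros.
- The opening reference to transfusion rates does not define a binary endpoint, and the protocol's outcome list is not shown. The absence of an any-RBC outcome from Table 2 is therefore not an error in itself.

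All of this stands, and it limits the point. A reader might infer that the plan commits these outcomes to a log ratio, or that its methods will in general reverse the saving in blood. The text supports neither. What remains is that, once the default is set aside, no all-patient effect measure is fixed, no zero rule exists for units, and the choice is made after seeing the data.

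**Conclusion.** The concern holds in this limited form. The default analysis of RBC units is sound; the fallbacks are not fixed well. A geometric-mean ratio is either undefined or set by the way zeros are handled, and a ratio among transfused patients is not a randomized comparison. In the illustrations the positive part alone understates the saving (0.87 against 0.52) or, for some distributions, reverses it (1.17 against 0.58). The size in this trial cannot be derived, because the share of zeros by arm is not given and depends on adherence and on whether pre-randomization units count. The outcome is secondary, and neither the primary analysis nor the sample size is affected. The change should be made because it removes a data-driven choice at almost no cost.

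**What to change.** For RBC units:

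- Keep the adjusted difference (or ratio) in arithmetic mean units across all analysed patients, zeros included, whatever the residual check shows. Use robust or bootstrap standard errors, or a log-link count model with robust errors.
- Remove the geometric-mean option for this outcome.
- Add the proportion given at least one RBC unit after randomization as a binary comparison.
- If a two-part model is fitted, report both parts or their combined mean, and label the positive part alone as descriptive.
- State whether units given before randomization count.

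The same all-patient mean can serve for plasma, platelets and cryoprecipitate, since zeros defeat the log there too, although the thresholds do not produce unequal zeros for them.

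The cost is a few lines of plan wording and a standard model; no new data are needed. One small downside is that an arithmetic mean is sensitive to a few heavily transfused patients, so the interval may be wider. The Discussion says the plan has since been executed. For this trial, the practical form is therefore to present the all-patient mean comparison and the any-RBC proportion beside whatever was reported.
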